#### Questionnaires

The questionnaires contain standard and validated measures. They include sociodemographic information (i.e., sex, ethnicity, work-related factors [seniority, weekly working hours]), health and behavior (i.e., MSP) [34], medicine use, smoking, general health [35], self-efficacy [36], fear avoidance [37], well-being [38], self-rated physical capacity (aerobic fitness, muscle strength, balance, endurance, flexibility) [39], stress [40] and work environment factors (i.e., perceived physical exertion during work) [41], pain-related work interference [34], noise, psychosocial work environment measured by the Danish Psychosocial Questionnaire (new questionnaire that is currently in the process of being published), work ability [42], need for recovery [43], and sickness absence and presenteeism [44–46].

### Anthropometric measures, grip strength, and blood pressure

To assess the health of the participants at baseline, objective physical measures of body height (Seca 213; Seca GmbH, Hamburg, Germany), body weight, body fat percentage (BC-418 MA body composition analyzer; Tanita, Tokyo, Japan), body mass index (body weight [kg]/(body height [m^2^]), grip strength (Jamar NC70144; North Coast Medical, USA), and blood pressure (Omron M3 or Omron M6 Comfort; Omron Corporation, Kyoto, Japan) will be performed. Participants receive individual feedback on the results of the measurements.

### Physical activity

#### Body postures and movements

Technical measurements of physical activity type (e.g., walking, climbing stairs, running), postures (e.g., arms above shoulder height, bending of the back), body position (e.g., standing, sitting, kneeling, and lying), and steps will be performed using the validated Acti4 software [47, 48] using AX3 accelerometers (3-Axis Logging Accelerometer; Axivity Ltd., Newcastle upon Tyne, UK). Objective measures for twisting of the back will be performed by the Acti4 software and GT9X (GT9X Link; ActiGraph LLC, Pensacola, FL, USA) inertial measurement unit (IMU). Acti4 has been validated for estimation of physical activity types, postures, and movements in semistandardized settings and in free living [47–50].

The AX3 accelerometer provides measurements of linear accelerations in three dimensions with a dynamic range of ± 8 G, sampled with a precision of 13 bits. The AX3 accelerometers will be initialized for recording, and data will be downloaded using the manufacturer’s software (OMGUI Version 1.0.0.30; Axivity Ltd) at a sampling rate of 25 Hz. The GT9X provides nine-component motion sensing by measuring acceleration in three dimensions with a dynamic range of ± 16 G, angular velocity in three dimensions with a dynamic range of ± 2000 degrees/s, and magnetometer heading in three dimensions with a dynamic range of ± 4800 μT. The GT9X IMUs will be initialized for recording, and data will be downloaded using the manufacturer’s software (ActiLife version 6.13.3; Actigraph LLC) at a sampling rate of 100 Hz. The AX3 and GT9X will be mounted on the skin with adhesive tape (Hair-Set double-sided adhesive tape; 3M Company, Maplewood, MN, USA) and secured with transparent adhesive film (OPSITE FLEXIFIX; Smith & Nephew plc, London, UK).

Five AX3 accelerometers will be mounted for 4–5 days at the following positions:The trunk, at one of two positionsThe spine just below the processus spinosus at the level of T1-T2On the midline of the flat part of the manubrium of the sternumThe dominant arm, laterally and 3 cm distal to the deltoid insertionThe right thigh at the most muscular part of the quadriceps femoris, midway on the line between the anterior inferior iliac spine and the top of the patellaRight and left calf, on the flat part of the soleus and gastrocnemius aponeurosis just distal to the lateral and medial heads of the gastrocnemius

Two GT9X IMUs will be mounted for 1 work day at the following positions:Upper back, on the spine just below the processus spinosus at the level of T1-T2 (just distal to the AX3)Lower back, on the spine at the level of L5-S1

The AX3 accelerometers and GT9X IMUs will be mounted with a spatial orientation of the accelerometer as described previously [47], with the *x*-axis being vertical and perpendicular to the skin surface with the positive *x*-axis pointing downward, the *y*-axis being horizontal and perpendicular to the skin surface with the positive *y*-axis pointing to the left, and the *z*-axis being horizontal and orthogonal to the skin surface with the positive *z*-axis pointing outward from the skin surface.

### Heart rate and heart rate variability measures

The measurements of heart rate and heart rate variability will be performed using Actiheart monitors (Actiheart; CamNtech, Cambridge, UK). The Actiheart is validated for measurement of heart rate and heart rate variability [51–53]. Actiheart measures raw electrocardiographic (ECG) signals with a sensitivity of 0.250 mV, which is electronically amplified by a factor of 900 (amplifier frequency response, 10–35 Hz). The resulting ECG signal is sampled at a frequency of 128 Hz, and each R-wave decaying edge is identified by using the Pan-Tompkins real-time QRS detection algorithm [54]. The Actiheart is configured to “short-term recording,” in which each interbeat interval (IBI) between consecutive detected R peaks in the QRS complex is stored for approximately 440,000 heartbeats. Before attachment, the skin will be shaved if necessary (Wilkinson Sword disposable hospital razor; Edgewell Personal Care, St. Louis, MO, USA) and gently rinsed with alcohol swabs (70% isopropyl alcohol). The Actiheart will be mounted with Ag/AgCl pregelled electrodes (Ambu BlueSensor VL-00-S/25; Ambu A/S, Ballerup, Denmark) at one of the two validated positions [55]:The apex of sternum with a horizontal wire to the right at the level of the fifth and sixth intercostal spaceThe manubrium of the sternum with a horizontal wire to the right at the level of the second and third intercostal space

The Actihearts are initialized for recording, and data are downloaded using the manufacturer’s software (Actiheart 4, version 4.0.116; CamNtech). The Actiheart IBI recordings will be processed in the Acti4 software to derive heart rate (HR) and heart rate variability (HRV) features using robust period detection [47].

### Observational measures

Visual workplace observations will be carried out following a standardized manual for observation to capture physical activities we are unable to capture by objective measurements (e.g., lifting, carrying and physically supporting a child, as well as squatting and sitting on the floor). Additionally, observations will capture contextual information from situations (e.g., diaper change, clothes change) and barriers to work (e.g., disturbances). Visual observations of large body postures and work activities are shown to have reasonable reliability among trained observers [56]. The observations will be carried out using a modified TRAC (task recording and analysis on computer)/portable ergonomic observation approach [57, 58]. In short, continuous observation will take place using a handheld computer (GT-P3100 or SM-T280; Samsung, Suwon, South Korea) with Pocket Observer software (Pocket Observer version 3.3.46; Noldus Information Technology, Wageningen, The Netherlands) to record start-stop or occurrence of observed items. The Pocket Observer recordings will be processed using The Observer XT software (The Observer XT version 14; Noldus Information Technology) to derive duration and frequency of observed items.

### Outcomes

#### Primary outcome measures

The primary outcomes of this study are (1) self-rated physical exertion measured on a Likert scale (0–10) [41] every 4 weeks by questionnaire from baseline to 4 months and (2) MSP (duration, intensity, and number of pain regions and pain-related work interference) measured every 4 weeks by questionnaire from baseline to 4 months.

#### Secondary outcome measures

Secondary outcomes of this study are (1) self-reported sickness absence due to MSP (days) measured by questionnaire every 4 weeks from baseline to 4 months, (2) objectively measured occupational physical activities by accelerometers and heart rate monitor at baseline and at 4 months, (3) self-efficacy measured by questionnaire at baseline and at 4 months, (4) need for recovery measured by questionnaire at baseline and at 4 months, and (5) employee involvement measured by questionnaire at baseline and at 4 months. Figure 4 shows the Standard Protocol Items: Recommendation for Interventional Trials (Additional file 1: SPIRIT) [59] schedule of enrollment, interventions, and assessments.

**Fig. 4 Fig4:**
[figure not shown]
Standard Protocol Items: Recommendation for Interventional Trials (SPIRIT) schedule of enrollment, interventions, and assessments [59]. *The randomization was carried out at workplace level before baseline measurements. However, the childcare workers were only told when their intervention started, with no mention of being in a control group or not. **The study uses a wait-list design, so that the control group receives the intervention after the immediate intervention group

#### Power calculation

For the power calculation, we used the calculation for a clustered parallel group with before-and-after measures to calculate the design effect [60]. Statistical power analysis was performed for primary outcome measures. The scale for self-rated physical exertion (0–10) has a mean of 4.09 and an SD of 2.41 in a representative sample of childcare workers in Denmark (*N* = 1137) [5]. The intracluster correlation coefficient (ICC) was calculated on the basis of a previous participatory ergonomics intervention among eldercare workers [61]. With a power of 0.80, an alpha of 0.05, a fixed cluster size of 12, and an estimated ICC of 0.005, we need 192 participants (96 per group) corresponding to approximately 16 clusters to statistically demonstrate a relevant effect in physical exertion of 1 point [60]. We also tried to vary the cluster size between 9 and 20 and check for differences in changing the values of ICC, which did not change the anticipated power very much. Because this is an organizational intervention, we expect only a small number of dropouts. In addition, the intervention period is quite short. We therefore expect to include 10% more than needed according to our power calculations, so that at baseline we will include approximately 210 participants. Additional power calculation for MSP showed that the numbers needed are within the same range as calculated for physical exertion.

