#### Randomization and blinding

All childcare institutions gave initial agreement to participate before we did the randomization. Because the intervention is group-based, and to avoid contamination between workers, cluster randomization was performed, with each childcare institution constituting a cluster. The randomization was balanced on institution size. Childcare institutions with 9–24 workers were stratified according to size to include an equal number of small (9–12 workers) and large (12+ workers) institutions. Within each size grouping, institutions were randomly allocated to either group 1 (early participatory ergonomics intervention) or group 2 (initial control group and late participatory ergonomics intervention group). The study was dimensioned to enroll approximately 200 workers (*see* the “Power calculation” section below). Because there were 29 institutions willing to participate with a total of approximately 400 workers, not all institutions could be offered an opportunity to participate in the study. In case some institutions dropped out before baseline data collection, we chose to randomize all 29 institutions so that we could replace that institution with another comparable institution. Thus, each institution was assigned a randomly drawn unique priority number between 1 and 100 and subsequently ranked within each group (InterventionSmall, ControlSmall, InterventionLarge, ControlLarge) with smaller number equaling higher priority. Finally, pairs were drawn until we reached the desired number of workers as demanded by the power calculation.

An independent data manager performed a computer-generated randomization using SAS for Windows statistical software (SAS Institute, Cary, NC, USA) developed by an independent statistician. Blinding of participants is not possible, owing to the nature of the trial. However, data collection will be performed using text messages, and persons collecting/handling data will be blinded to group allocation.

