### Statistical analyses

Baseline characteristics will be described by questionnaires and the anthropometric measures. Analyses regarding the effectiveness of the primary outcomes and secondary outcomes will be performed after 4 months of intervention with multilevel analyses. Multilevel analyses take clustering of observations of workers within the same team into account, as well as repeated measurements within one participant [66]. All analyses will be performed according to the intention-to-treat principle, including all eligible randomized participants without imputations because mixed models inherently account for missing values [67]. Both the immediate intervention group and the delayed intervention group will be followed with questionnaires and objective measurements after the delayed intervention group has received the intervention. It is expected that during this time, the immediate intervention group will continue with the intervention activities. This allows for longer follow-up for the immediate intervention group and the possibility to do a secondary analysis of long-term follow-up. However, due to the design of the study (two-arm cluster-randomized design employing a wait-list control), no untreated control group exists at the measurement after 8 months, and follow-up effects will thus be uncontrolled and modeled using data from intervention participants only (Fig. 1).

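### The 192 participants are credited to a before-and-after design effect, but no baseline to follow-up correlation is given, so the stated 80% power cannot be tied to the named method

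*Protocol article*

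**What the plan says.** The Power calculation section names its method: "we used the calculation for a clustered parallel group with before-and-after measures to calculate the design effect". For physical exertion on the 0 to 10 scale, it reports that the measure "has a mean of 4.09 and an SD of 2.41 in a representative sample of childcare workers in Denmark". The other inputs follow: "With a power of 0.80, an alpha of 0.05, a fixed cluster size of 12, and an estimated ICC of 0.005". The result is that "we need 192 participants (96 per group) corresponding to approximately 16 clusters" "to statistically demonstrate a relevant effect in physical exertion of 1 point". The section adds that cluster size and ICC were varied with little effect on power, and that recruitment is raised to about 210 to allow for dropout. No correlation between baseline and follow-up appears, either as an input or among the quantities varied.

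The Statistical analyses section plans a comparison after 4 months by multilevel models: "Multilevel analyses take clustering of observations of workers within the same team into account, as well as repeated measurements within one participant". It does not say how the baseline value enters. Under Primary outcome measures, exertion and pain are collected every 4 weeks, starting at baseline. Under Randomization and blinding: "The randomization was balanced on institution size", with small and large institutions allocated separately.

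**The concern.** A before-and-after calculation multiplies the after-only sample size by a factor that depends on r. The factor is 1 − r² if baseline is a covariate and 2(1 − r) if change from baseline is compared. Without r, neither version can be computed. Yet the section reaches a definite number, and its listed inputs are enough to produce that number with no correlation at all. Either the before-and-after feature played no part, and the method is misdescribed, or it entered through an unstated assumption that decides the result.

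What is at stake is the meaning of the 80%. Depending on how baseline is handled, the same 192 participants can have clearly more or clearly less power than stated, and the article does not let a reader say which.

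**Working it through.** **Inputs from the Power calculation section:** SD 2.41, difference 1 point, power 0.80, alpha 0.05, cluster size 12, ICC 0.005. Two-sided alpha is assumed because the article does not state sidedness; one-sided alpha gives about 76 per arm and does not reproduce the figure.

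**Step 1: reproduce the stated size.**
- Per arm without clustering: 2 × (1.96 + 0.8416)² × 2.41² / 1² = 91.17.
- After-only design effect: 1 + (12 − 1) × 0.005 = 1.055.
- Per arm with clustering: 91.17 × 1.055 = 96.19. The total is 192.4, or 96.19 / 12 = 8.02 clusters per arm.

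These are the stated 96, 192 and 16, to rounding. (Strict rounding up would give 97 per arm and 194.)

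**Step 2: see what a before-and-after calculation would give.** The total becomes 192.4 × (1 − r²) with baseline as covariate, or 192.4 × 2(1 − r) for a change score. The values of r are assumptions.

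| r | Covariate: total N | Change score: total N |
|---|---|---|
| 0.3 | 175 | 269 |
| 0.5 | 144 | 192.4 |
| 0.7 | 98 | 115 |

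The covariate version gives fewer than 192 for any r of practical size. The change-score version gives 192.4 only at r = 0.5, where 2(1 − r) = 1.

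**Step 3: power with 96 per arm.** The standard error of the after-only difference is 2.41 × √(2 × 1.055 / 96) = 0.357. Power is Φ(1 / (0.357 × √factor) − 1.96).

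| r | After-only (factor 1) | Covariate (1 − r²) | Change score (2(1 − r)) |
|---|---|---|---|
| 0.3 | 0.80 | 0.84 | 0.66 |
| 0.4 | 0.80 | 0.86 | 0.72 |
| 0.5 | 0.80 | 0.90 | 0.80 |
| 0.6 | 0.80 | 0.94 | 0.88 |

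Strictly, r here is the correlation of institution means. At an ICC of 0.005 it is close to the correlation within a worker: a within-worker value of 0.3 gives 0.31 to 0.34 when the cluster autocorrelation is between 0.5 and 1.

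**Step 4: compare the two uses of baseline.** 2(1 − r) − (1 − r²) = (1 − r)², which is never negative, and 1 − r² never exceeds 1. So, degrees of freedom aside, covariate adjustment is at least as precise as either alternative at every r.

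**The case against.** The case against has several parts.

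- **The listed inputs do reproduce 192.** This is right: there is no arithmetic error. The gap lies between the method named and the inputs given.
- **The match does not prove that baseline was ignored.** This also stands. A change score at r = 0.5 gives the same total, and the source cited for the formula is not available here. A reader might infer that 192 must be an after-only number; the article leaves that open.
- **No change-score analysis is proposed.** A reader might infer from the 0.66 that the trial is underpowered. The article does not support that. Baseline may enter the multilevel model as one of the repeated outcomes. With two time points, complete data and baseline means free to differ by arm, the contrast of 4 months with baseline equals the change score. With a common baseline mean, precision is close to the covariate version. If the effect is averaged over four equally correlated follow-ups, the change factor is (1 + 3r)/4 − 2r + 1. That is 0.875 at r = 0.3 and exceeds 1 only for r below 0.2.
- **Covariates are commonly left to the analysis plan.** This is correct. Their absence from a condensed article is no finding.
- **Chance imbalance at baseline is not an extra risk.** A baseline difference between arms with an SD of about 0.36 points sounds large beside a 1-point target. But it is the same 0.357 standard error as in step 3, and the power figure already allows for it. Adjustment gains precision; it does not repair a bias.
- **Recruitment ended in November 2017.** Restating power cannot change enrolment.

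What survives is the mismatch between the named method and the listed inputs. An analysis plan would not normally settle it, because the method and the number stand together in this section.

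**Conclusion.** The point holds in a limited form. The article attributes 192 to a before-and-after design effect without the correlation that such a design effect needs, and the number follows without one. The stated 80% is about right for an after-only comparison, conservative with baseline as a covariate (0.84 to 0.94 for r from 0.3 to 0.6), and optimistic only for a change-from-baseline contrast at 4 months with r below 0.5. In that last case power would be about 0.66 at r = 0.3, and 269 participants would be needed against about 210 planned.

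It would go too far to say that the stated power fails to describe the analysis: an analysis that does not use baseline would match it.

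The figures rest on two-sided alpha, assumed values of r, the article's SD and ICC, and the normal approximation that reproduces 192. With a t reference on 16 − 2 = 14 cluster-level degrees of freedom, after-only power would be about 0.74, so all the figures above are somewhat generous in absolute terms.

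**What to change.** **Correct the Power calculation section.** Either state that 192 is the after-only size, using the design effect 1 + 11 × 0.005 = 1.055, or give the assumed baseline to 4-month correlation and the form of analysis, and recompute. This costs one paragraph.

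**Improve the primary model.** Adjust for the baseline value of each outcome and include the institution size stratum as a fixed effect, alongside the random effects already planned. Then restate power for that model over r from 0.3 to 0.7. If the analysis plan already does this, only the restated power is needed.

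The data are already being collected. The cost is about one cluster-level degree of freedom for the stratum, roughly 14 to 13. One caveat: the Data collection section places baseline after randomization but before the intervention. Adjustment therefore assumes that knowing the start date did not shift the baseline answers; a change score needs the same assumption.

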### Economic measures

#### Health-related production loss

Presenteeism (reduced performance while being present at work) and absenteeism (hours and days missed from work due to sickness absence) will be measured by questionnaire every 4 weeks [44, 45]. In addition, sickness absence data (absenteeism) will be retrospectively collected from company records after the last follow-up measurement.

#### Cost measures

Intervention costs include the costs for workshops (i.e., costs for the consultant [including preparation], time spent on the workshop by the participants, and materials), and costs for meetings with the workplace in preparation for the project, as well as costs for fruit and snacks offered at these meetings and printed materials. Consultants’ and participants’ costs will be valued on the basis of their salary. Other costs will be valued using invoices. Workplace productivity losses (i.e., presenteeism and absenteeism) will also be valued using salaries of the participants.

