#### Intervention content: participatory ergonomics

Participatory ergonomics covers “the involvement of the workers in planning and controlling significant amount of their own work activities, with sufficient knowledge and power to influence both processes and outcomes to achieve desirable goals” [10]*.* The literature highlights participatory ergonomics as being not a unitary concept, but rather an umbrella term covering a broad range of ideas and practices [11]. In this study, inspiration from the framework suggested by Haines and colleagues [11] as well as the blueprint suggested by Wells and colleagues [33] was used in the development of the participatory ergonomics intervention. Therefore, the participatory ergonomic process follows 6 steps: (1) identification of risk factors, (2) analysis of risk factors, (3) solution building, (4) prototype implementation, (5) evaluation of prototype, and (6) adoption of a solution. These steps will be carried out in one workshop of 3 hours and two follow-up workshops of 1.5 hours (Fig. 3). A main feature of this participatory ergonomics intervention is the integration with the core work tasks as previously recommended for improving implementation [17].

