### Control

Those in the initial control group will continue their usual practice from baseline to the 4-month follow-up. Usual practice in this type of workplace is ergonomic consultancy and guidance or individual advice on pain management from therapists (physiotherapists or occupational therapists) employed in the municipality. Each workplace or worker can contact a therapist if they feel that they need it. It is not possible to collect information on an individual level with respect to use of a therapist, but we will have information on a workplace level whether they have contacted the therapists for ergonomic consultancy and guidance. This group will receive the intervention after the 4-month follow-up.

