### Economic evaluation

The economic evaluation aims to determine the cost-effectiveness of the intervention compared with usual care from the employer’s perspective. In addition, a cost-benefit analysis will be performed from the employer’s perspective. Analyses will be performed according to the intention-to-treat principle with multiple imputation of missing data [62, 63]. Sensitivity analyses will be done to assess the robustness of the results. The total employer’s costs of the intervention will be estimated and compared between the intervention and control groups. The 95% CIs will be estimated using approximate bootstrap CIs [63]. For the cost-effectiveness analysis, incremental cost-effectiveness ratios will be calculated by dividing the mean difference in costs between both groups by the difference in effects on the primary outcome measures self-rated physical exertion and MSP. Cost-effectiveness planes will be graphically presented [62]. In addition, a cost-benefit analysis will be performed in which the incremental intervention costs will be compared with the incremental productivity-related costs. This will be expressed as return on investment as well as benefit-to-cost ratio.

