Because this is an organizational intervention, it does not focus on individual workers. Thus, individual randomization is not feasible. Our trial lacks allocation concealment and will be at risk of selection biases. However, we will check and report any evidence of selection bias by comparison of the proportion that participated at each institution and compare characteristics (by using information from the payroll) of participants and nonparticipants. Moreover, due to the interventional trial design, participants cannot be blinded to group allocation. However, all participating childcare workers would receive the intervention and are only told when their intervention is intended to start with no mention of being in a control group. This minimizes the potential selection bias. However, outcome assessors and data analysts will be blinded to group allocation. A possible limitation is the short follow-up duration, because the effect of workplace changes may take longer time to set in (4 months). In addition, the use of a wait-list design could imply a risk of implementing a noneffective intervention for the control arm, which will have cost and resource implications. Our experience with such interventions is that the process, no matter the statistical effect, will benefit the workers, and the workplaces need to plan these interventions a long time ahead and promise the employees that they will receive the intervention.

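### The return on investment adds presenteeism self-rated by unblinded workers to absence of unstated source, and a reporting shift of roughly 1 to 2 percentage points could decide between loss and profit

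*Protocol article*

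**What the plan says.** Under Health-related production loss, presenteeism and absenteeism are both measured by worker questionnaire every 4 weeks. A second source is then given for absence only: "In addition, sickness absence data (absenteeism) will be retrospectively collected from company records after the last follow-up measurement".

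Under Cost measures, the two components are valued in the same way: "Workplace productivity losses (i.e., presenteeism and absenteeism) will also be valued using salaries of the participants". The programme's own cost covers "costs for the consultant [including preparation], time spent on the workshop by the participants, and materials", plus preparatory meetings, refreshments and printed matter. On valuation the section says: "Consultants’ and participants’ costs will be valued on the basis of their salary". No amounts are given.

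Under Economic evaluation, incremental intervention costs are set against incremental productivity-related costs: "This will be expressed as return on investment as well as benefit-to-cost ratio". Bootstrap intervals and sensitivity analyses are promised; the content of the sensitivity analyses is not described.

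On blinding, Strengths and limitations of the study accepts that "participants cannot be blinded to group allocation". It adds that workers are told only when their programme starts and are not told that they are controls.

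**The concern.** The person who rates presenteeism is the worker, so blinding the data handlers and analysts does not protect that measurement. Workers who have sat through three workshops know it when they rate their own performance. Because presenteeism and absence enter as one productivity total, the ratios as described do not show whether a profit comes from fewer recorded sick days or from a changed self-rating.

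The programme is also cheap per worker, while presenteeism, once valued at salary, can apply to every hour worked. A small movement in the rating may then outweigh the whole cost.

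The absence component is not settled either. The secondary outcome is self-reported absence, whereas the abstract refers to company records. If questionnaire absence is what is valued, the entire benefit side is unblinded self-report. What is at stake is the conclusion offered to employers.

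**Working it through.** The article states no break-even or return figure, so there is none to reproduce.

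**Inputs from the article**
- Workshop time: "one workshop of 3 hours and two follow-up workshops of 1.5 hours", so 3 + 1.5 + 1.5 = 6 h per worker.
- Controlled period: "Those in the initial control group will continue their usual practice from baseline to the 4-month follow-up". Four months is taken as 16 weeks (17.3 calendar weeks at most).
- Worker time and productivity losses are both valued at salary.

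**Assumptions, none of them in the article**
- Presenteeism is converted to a share of paid hours.
- The working week is 30–37 h, so paid hours H = 16 × 30 = 480 to 16 × 37 = 592 per worker.
- Consultant hours, wage ratio, group size and materials are as shown below.

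**Formula.** Let C be the programme cost per worker in worker-hour equivalents. The worker's wage appears on both sides and cancels, so the break-even shift in presenteeism is C / H.

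**Worker time only.** 6/592 = 1.0% and 6/480 = 1.25%. Using 17.3 weeks at 37 h lowers the first figure to 0.94%.

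**Whole programme.** C = 6 + r × (6 + p)/m + k. Here 6 + p is consultant hours (delivery plus preparation and meetings), r is the consultant's wage relative to the worker's, m is the number of workers sharing the consultant, and k is materials in hour equivalents. H is for 16 weeks.

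| h/week | m | p | r | k | C (h) | C/H |
|---|---|---|---|---|---|---|
| 37 | 12 | 0 | 1 | 0 | 6.50 | 6.50/592 = 1.1% |
| 37 | 12 | 6 | 1 | 0 | 7.00 | 7.00/592 = 1.2% |
| 37 | 12 | 10 | 1.25 | 0.25 | 7.92 | 7.92/592 = 1.3% |
| 30 | 12 | 12 | 1 | 0 | 7.50 | 7.50/480 = 1.6% |
| 32 | 12 | 16 | 1.5 | 0.25 | 9.00 | 9.00/512 = 1.8% |
| 32 | 9 | 16 | 1.5 | 0.25 | 9.92 | 9.92/512 = 1.9% |

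Once some preparation or meeting time is counted, the figure runs from about 1.2 to 1.9 points. The last row at 30 h/week would give 9.92/480 = 2.1%. Two consultants or heavier preparation would raise it further. On a 0–10 rating, if that is the scale, 1.0–1.9 points is 0.10–0.19.

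**The same cost in absence.** With a 7.4 h day (37/5), 6/7.4 = 0.8 and 9.92/7.4 = 1.3 sick days per worker.

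**Against sampling error (illustrative).** Take the plan's 96 per group, its design effect 1 + 11 × 0.005 = 1.055, and an assumed presenteeism SD of 10–25 points. The standard error of a single-wave difference is SD × √(2 × 1.055/96), or 1.5–3.7 points. The break-even shift is of the same order as this standard error or smaller.

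**The case against.** Several points on the other side have force.

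- This is a condensed article. A full economic analysis plan could name the absence source, define the sensitivity analyses and break down the components. That stands as a reason for moderation. However, the article itself fixes the components, the valuation and the summary ratios, and the point is directed at that stated combination.
- Valuing both components at salary is a coherent choice from the employer's perspective. That stands, which is why presenteeism should be kept and shown rather than dropped.
- A low break-even reflects a cheap programme. About one sick day per worker would also repay it, so absence can move the ratio too. That is correct, but recorded absence is not open to the same reporting bias.
- Bootstrap intervals would probably show that a 1–2 point shift is not distinguishable from zero. They describe sampling error, however, and leave bias in place.
- Telling workers only their start date lowers the risk of differential expectation. It does not remove it.

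A reader might go further and infer that expectation alone will produce a profit. For example, a 3-point shift with no true effect would give a ratio of 0.03 × 480/7.5 = 1.9 to 0.03 × 592/7 = 2.5. The documents do not support that. The 3 points are invented and would have to hold in full from the first day, although the workshops are spread over the 4 months. If the shift built up linearly, the average would be 1.5 points and the ratio 0.96–1.27, close to break-even. A reader might also infer that questionnaire and recorded absence will be summed, or that components will be withheld from the report. The article says neither.

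**Conclusion.** The point holds in a limited form. The planned ratios rest on one productivity total that mixes an unblinded self-rating with absence of unstated source, and none of the stated safeguards separates reporting bias from a real gain.

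The only part of the size that comes close to following from the article is worker time: 6 h over about 16 weeks, or 1.0–1.25 percentage points at an assumed 30–37 h/week. The programme as a whole needs about 1.2–1.9 points under assumed consultant, preparation and meeting costs. Both figures also assume that presenteeism is valued as a share of paid hours. The order of magnitude, 1 to 2 points, is stable across ordinary assumptions; the exact range is not.

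The supported conclusion is that a reporting shift of this size could decide between loss and profit. Whether such a shift will occur, and how large it would be, cannot be judged from the documents. This is a cheap improvement to the economic reporting and does not bear on the primary effect analysis.

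**What to change.** In Cost measures and Economic evaluation:

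1. Make company records the main source for valuing absence. Use questionnaire absence as a sensitivity analysis and never add it to recorded absence.
2. Report return on investment and benefit-to-cost ratio side by side for (i) recorded absence alone and (ii) recorded absence plus self-rated presenteeism.
3. State how presenteeism is converted to money, and give the presenteeism change at which the programme breaks even, calculated from the actual costs.
4. State in advance that a positive return seen only in (ii) will be described as resting on unblinded self-report.

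All the data are already planned, so the cost is some wording and one extra column of results. The absence-only ratio leaves out any genuine presenteeism gain, and possibly part-day absence if company records do not capture it. That is why both columns and the questionnaire sensitivity analysis are kept.
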